#### Randomisation Procedures

Eligible parents will be randomised to either the parent intervention group or the W-L group. This will typically occur between three and four months post their child's diagnosis.

Three randomisation lists will be generated, one list per participating department. This will enable separate analysis by illness group as well as an overall exploration of outcomes for families of children with SCII. Each randomisation list will contain twenty six spaces. Participants will be randomly allocated to one of the two treatment arms using The RCH Department, Clinical Epidemiology and Biostatistics Unit (CEBU), computerised randomisation plan generator. This program will randomise each participant to one of the two treatment arms using the method of randomly permuted blocks. The end result will be two randomly allocated treatment arms of equal size divided between three randomisation lists organised according to Hospital Department (Cancer, Cardiac and PICU).

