### Parent Intervention Participants

One hundred and eighty four families will be allocated to each of the two treatment arms. A potential total of 263 eligible parents are required, as we anticipate that 50% of eligible families will either be uncontactable, refuse to participate, or their child's illness will exclude them from participating at this later stage. See Figure 3 for participant flow details.

[figure not shown]

Figure 1: Recruitment, assessment & participant flow

Figure 3: Recruitment, assessment and participant flow

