### Eligibility Criteria

#### Inclusion Criteria

To be eligible to participate parents must meet all of the following criteria:

1. Parents must have a child aged between zero and eighteen years during their first presentation treatment for a SCII (cancer, cardiac disease or who have been admitted to hospital in the PICU department)
  - Cardiac – child required surgery within the 1st month of life. This decision was made following consultation with the Head of Cardiology who recommended that we target this group of parents as they are more likely to be traumatised compared to other parents of children with cardiac disease.
  - Cancer – all cancer types
  - PICU – child's stay at PICU must be greater than or equal to 48 hours
2. Parents may be male or female

- 313 3. Both mothers and fathers can participate together or individually, however the  
314 eligible parent must take part
- 315 4. Parents must have an active and current parenting role with the child (defined  
316 as the person(s) who perceives that they have an active parenting role)
- 317 5. Parents must be able to comply with the study intervention and assessment  
318 protocols. This will be determined by the researcher during registration contact  
319 with the parent
- 320 6. Parents may have multiple children diagnosed with an SCII
- 321 7. Parents must be over 18 years

322  
323

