#### 7.4 Blinding Arrangements

Research team members responsible for recruiting families to the study or delivering the TAB intervention to families will be blind to the randomisation list. No researcher involved with recruitment or clinical delivery will have access to the randomisation list, thereby ensuring they are blind to client allocation and ensuring the randomness of allocation. A research officer, not involved in either the recruitment process or clinical delivery, will manage the randomisation list. When a consent form is received the research assistant responsible for recruitment will contact the research officer to have the participant placed on the randomisation list for the correct department using their subject identification code.

The research assistant will be informed of the allocation and will then contact the parent to discuss the allocation and plan their enrolment in a group as described above.

Researchers conducting the data analysis will be blind to participant identity and allocation. Analysis will be conducted on re-identifiable data only. A research assistant not responsible for analysis will conduct a re-identification of participant if needed.

Participants will be partially blinded. That means that participating parents will know if they have been randomised to W-L or the parent intervention arm (TAB) once they have been advised whether they will receive the intervention immediately or in two-six months' time.

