### **11.3 Statistical Analysis Plan**

Demographic, illness group (oncology, PICU, cardiac) and screener characteristics will be compared between groups. For parent-level data (for couples that were both eligible), categorical variables will be compared using Generalised Estimating Equation (GEE) models to account for within-couple correlation (with the exception of parent sex and illness group). A GEE with a Gaussian distribution will be employed to compare group means of the screening measure. Time between measurements using linear regression models, and illness group distributions will be compared using a chi-squared test.

GEE models will compare mean outcome measures between groups at T3, and GEE models will also account for within-couple correlations. Effect size Cohen's d will be calculated, and interpreted as small<0.2, medium>0.2-0.5, large=>0.5-0.8, very large >0.8 (Cohen, 1988).

Further analyses will include exploration of the predictors of intervention outcome, and a thorough analysis of treatment adherence, compliance with intervention and other process variables. Detailed descriptive analysis of pre-intervention child, parent and family characteristics will also be conducted to thoroughly explore the characteristics of families attending a parent focused, psychosocial intervention.

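### The unit of randomisation is not fixed (participant or family), so two eligible parents of one child could be placed in opposite arms and the wait-list parent exposed to TAB through the partner

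*Protocol*

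**What the plan says.** **Text that points to the individual.** Randomisation Procedures: "This program will randomise each participant to one of the two treatment arms using the method of randomly permuted blocks". The only stratification is by department: "Three randomisation lists will be generated, one list per participating department". Section 7.4 gives the working step. When a consent form arrives, the recruiting assistant contacts the research officer "to have the participant placed on the randomisation list for the correct department using their subject identification code".

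**Text that points to the family.** Section 4.3, Parent Intervention Participants: "One hundred and eighty four families will be allocated to each of the two treatment arms". In the Recruitment steps for the RCT, item e has a family giving verbal consent, after which the parents are enrolled and allocated. It does not say that they are allocated jointly.

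**Couples are expected.** Inclusion criterion 3: "Both mothers and fathers can participate together or individually", provided that the eligible parent takes part. Section 11.3: "For parent-level data (for couples that were both eligible), categorical variables will be compared" by GEE, and the outcome models also use GEE to allow for within-couple correlation.

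**Control condition.** Section 5.1 gives wait-list parents standard hospital care until their post questionnaire. Section 8.2 times their assessments to match a TAB group.

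**The concern.** If partners can be allocated separately, some wait-list parents will live with someone who is taking the program during the comparison window. Section 5.1 encourages participants to practise its strategies between sessions, and the content covers family relationships, roles and activities. Part of the program could therefore reach the wait-list partner before T4. Any benefit passed on lowers the wait-list mean PCL-5 score and shrinks the difference between arms.

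The planned GEE deals with the correlation of two outcomes within a couple, so it affects standard errors. It does not remove a bias in the difference itself, and the protocol says nothing about contamination between partners. The unit of randomisation also belongs in the protocol, because whoever runs the lists needs it before the first couple consents.

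**Working it through.** **1. Is the unit settled by the text?** Randomisation Procedures and section 7.4 describe the procedure and name the participant. Section 4.3 names families, but that sentence cannot decide the matter: it puts 184 families in each arm, whereas section 7.6 and Sample Size Estimation give 184 participants in total. Item e of the Recruitment steps is compatible with either unit. The protocol is inconsistent, and no sentence keeps partners together.

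**2. How often would a couple be split under individual allocation?** With independent 1:1 allocation the probability is 0.5. If the two parents take consecutive places within one permuted block of size b, it is (b/2)/(b − 1):

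| Block size | Probability of a split |
|---|---|
| 8 | 4/7 = 0.57 |
| 6 | 3/5 = 0.60 |
| 4 | 2/3 = 0.67 |
| 2 | 1/1 = 1.0 |

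Block size is not given. Hence about half or more.

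**3. The plan's own figure.** Inputs from Sample Size Estimation: difference 6.0, SD 13.9, significance level 0.05 (taken as two-sided), 82 per arm. The two-sample t-test has power 0.785 (normal approximation 0.789), close to the stated 0.80. The normal formula 2 × [13.9 × (1.960 + 0.842)/6.0]² = 84.2 gives 85 per arm. That small shortfall is a separate matter.

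**4. Dilution.** Let f be the share of randomised parents who are in couples with both parents enrolled, and s the share of the TAB benefit that reaches a wait-list partner. With half of couples split, f/2 of wait-list parents have a partner in TAB, so

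expected difference = 6.0 × (1 − (f/2) × s).

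The protocol gives neither f nor s; the values below are assumptions.

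| f | s | Difference | Power at 82 per arm (t-test) |
|---|---|---|---|
| 0 | – | 6.0 | 0.785 |
| 0.2 | 0.5 | 6.0 × (1 − 0.05) = 5.7 | 0.74 |
| 0.4 | 0.5 | 6.0 × (1 − 0.10) = 5.4 | 0.70 |

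**5. Cost of allocating families.** The approximate design effect is 1 + f × ICC. With f = 0.4 and an assumed ICC of 0.3 it is 1 + 0.12 = 1.12. Effective size is 82/1.12 = 73 per arm, and power for an undiluted 6.0 points is about 0.74.

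**The case against.** The strongest reply is that the protocol means to randomise families. Section 4.3 says so, the Recruitment steps treat the family as the party that is invited and consents, and letting mothers and fathers take part together fits a shared arm better than a split one. This stands to the extent that a reader may not infer that couples will be split, or that half of them will be: the text is contradictory, not settled. It does not remove the point, because the two sections that describe how a slot is filled both name the participant, and no joint rule is stated.

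A second reply is that exposure through a partner is weak. The protocol encourages practice between sessions, but it does not say that participants practise at home or with the partner, and one parent's practice is not a facilitated nine-hour program for the other. This is fair, and it is why the spill-over must remain an assumption.

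A third reply is that few couples may enrol. Sections 4.3 and 7.6 assume 70% screening uptake, a 5% loss, 50% excluded as not distressed, and then 50% participation (or 184/263 = 0.70). If partners behaved independently, the chance that an enrolled parent's partner is also enrolled would be 0.70 × 0.95 × 0.50 × 0.50 = 0.17 to 0.70 × 0.95 × 0.50 × 0.70 = 0.23, before allowing for single parents. Partners' distress and willingness are likely to be correlated, which raises this, so it is not a ceiling. It does support the lower part of the range shown.

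**Conclusion.** The concern holds as an inconsistency with a consequence. The unit of randomisation is the participant in two sections and the family in another, couples are expected, and nothing keeps them in one arm. Under the participant wording, about half or more of the couples could be split, and any spill-over would bias the T4 PCL-5 difference towards zero in a way that GEE does not repair.

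The size cannot be computed from the protocol. With 20% to 40% of parents in couples and 50% spill-over, both assumed, the loss is 0.3 to 0.6 points and power falls from about 0.785 to between 0.74 and 0.70.

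A reader might go further and infer a collapse in power. With 60% of parents in couples and the whole benefit passed to a partner who never attended, the difference would be 6.0 × (1 − 0.30) = 4.2 and power about 0.49. Nothing in the protocol supports inputs that extreme. The point warrants a correction but does not show that the trial would fail.

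**What to change.** State in Randomisation Procedures that the family is the unit of randomisation, with one list slot per family and all eligible parents of that family in the same arm. The slot must be per family and not per child, because inclusion criterion 6 admits parents with several affected children, and such a family could otherwise be drawn into both arms. Add how a second parent who consents later is handled: that parent takes the family's existing allocation. Reconcile section 4.3, the Recruitment steps, Randomisation Procedures and section 7.4 with this, including the 184 per arm against 184 in total. Keep GEE, with family as the cluster.

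The change to the text and the lists is small. The statistical cost should be stated openly. At a design effect of 1.12, power at 82 per arm is about 0.74, so either the stated power is revised or the sample size is raised. Holding 0.80 would need 85 × 1.12 = 95.2, so 96 per arm before attrition. At the low-dilution end, family allocation gives no gain in power (0.74 either way at 5.7 points, though with different assumed couple shares). What it buys is an estimate free of dilution between partners.

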#### 7.4 Blinding Arrangements

Research team members responsible for recruiting families to the study or delivering the TAB intervention to families will be blind to the randomisation list. No researcher involved with recruitment or clinical delivery will have access to the randomisation list, thereby ensuring they are blind to client allocation and ensuring the randomness of allocation. A research officer, not involved in either the recruitment process or clinical delivery, will manage the randomisation list. When a consent form is received the research assistant responsible for recruitment will contact the research officer to have the participant placed on the randomisation list for the correct department using their subject identification code.

The research assistant will be informed of the allocation and will then contact the parent to discuss the allocation and plan their enrolment in a group as described above.

Researchers conducting the data analysis will be blind to participant identity and allocation. Analysis will be conducted on re-identifiable data only. A research assistant not responsible for analysis will conduct a re-identification of participant if needed.

Participants will be partially blinded. That means that participating parents will know if they have been randomised to W-L or the parent intervention arm (TAB) once they have been advised whether they will receive the intervention immediately or in two-six months' time.

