|                   | T3: Intervention      | 23 | Parent Program – Session 1                                                                                                                                                                    |
|                   |                                     | 24 | Parent Program – Session 2                                                                                                                                                                    |
|                   |                                     | 25 | Parent Program – Session 3                                                                                                                                                                    |
|                   |                                     | 26 | Parent Program – Session 4                                                                                                                                                                    |
|                   |                                     | 30 | Parent Program – Session 5
Parent Program – Session 6                                                                                                                                      |
|                   | T4: Post Intervention | 30 | Parent posttraumatic stress
Experience of illness
Child wellbeing
Child Psychopathology
Parent wellbeing
Parent Psychopathology
General Family Functioning
Acceptability |
|                   | T5: 6-month Follow-up | 58 | Same as pre-assessment measures only for intervention families                                                                                                                                |

509 Table 2. Implementation Schedule

510 **Screening Questionnaire**

511 *Acute Stress Disorder Scale (ASDS; R. A. Bryant, Moulds, & Guthrie, 2000)*

512 The ASDS is a 19-item self-report measure designed to assess acute stress disorders in  
513 individuals in the acute period (up to 4 weeks) following a traumatic event and who may  
514 be at risk of developing PTSD. The ASDS indexes acute stress disorder based upon the  
515 criteria of the Diagnostic and Statistical Manual of Mental Disorders 4th ed. (DSM- IV).  

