**Acceptability**

*Consumer Satisfaction Scale (Parenting Research Centre, 2010).*

The CSS is a measure of consumer satisfaction with parent training programs. It assesses the quality of the service provided; how well the program met the parent's needs and changed behaviour, and whether the parent would recommend the program to others. Parents are also prompted to make general comments or suggestions about the program. The instrument is included as a measure of parental perceptions of the program, the information provided by parents will be used to refine and improve the program. This measure will be completed at Time 4 (post program completion) only.

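### Section 7.4 declares recruiters blind to allocation, yet the recruiting assistant is told every allocation, so later allocations on a department list can be guessed better than chance

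*Protocol*

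**What the plan says.** Protocol 7.4 (Blinding Arrangements) states the safeguard: "No researcher involved with recruitment or clinical delivery will have access to the randomisation list, thereby ensuring they are blind to client allocation". It adds that this secures the randomness of allocation. An independent research officer, outside recruitment and delivery, manages the list.

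The procedure follows in the same section. When consent arrives, "the research assistant responsible for recruitment will contact the research officer to have the participant placed on the randomisation list for the correct department". Then: "The research assistant will be informed of the allocation and will then contact the parent to discuss the allocation and plan their enrolment in a" […].

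Randomisation Procedures sets up one list for each of three departments, with 26 spaces per list and arms of equal size, "using the method of randomly permuted blocks". Neither the block size nor whether it varies is given.

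For the analysts, 7.4 says: "Researchers conducting the data analysis will be blind to participant identity and allocation". Table 2 describes the six-month follow-up (T5) as "Same as pre-assessment measures only for intervention families". Of the satisfaction scale, the Acceptability section says: "This measure will be completed at Time 4 (post program completion) only".

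**The concern.** Not seeing the list is different from not knowing allocations. Section 7.4 treats the first as if it delivered the second, and then gives the recruiting assistant every result. Over time that person holds the running history of each department list. With balanced blocks, the history carries information about the next place.

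This matters because the recruiting side still acts before each randomisation. It makes the invitation call, decides how that call is conducted, and sets randomisation in motion when written consent arrives or, under item e of the RCT Recruitment section, on verbal consent. There is also a practical reason to care which arm comes next, since section 8.2 starts a TAB group only once at least five parents have been randomised to TAB. The primary outcome, the PCL-5, is self-reported by parents who know their arm, so blinded assessment cannot offset selection at entry. Concealment of upcoming allocations is the main protection left.

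**Working it through.** **The text set side by side (all from 7.4)**

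1. Premise: recruiters and facilitators have no access to the list.
2. Conclusion drawn: they are therefore blind to client allocation.
3. Procedure: the recruiting assistant asks for each allocation, is told it, and discusses it with the parent.

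Step 3 contradicts step 2 for recruiters. For facilitators, step 2 cannot be true because they deliver TAB to the parents in their groups. Step 1 is compatible with step 3, so what the procedure delivers is concealment of the list, not blinding to allocation.

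**How much the history reveals**

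The plan has no figure of its own to reproduce here. Inputs from Randomisation Procedures are 1:1 allocation, permuted blocks, three lists and 26 places per list. Assumptions are that one recruiter sees all past allocations on a list, and the block sizes tried below.

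For a fixed block of size 2b, a recruiter who always guesses the arm that is behind, and tosses a coin when the arms are level, is correct with average probability

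0.5 + (4^b / C(2b, b) − 1) / (4b).

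- Block of 2 (b = 1): 0.5 + (4/2 − 1)/4 = 75.0%
- Block of 4 (b = 2): 0.5 + (16/6 − 1)/8 = 70.8%
- Block of 6 (b = 3): 0.5 + (64/20 − 1)/12 = 68.3%
- Block of 8 (b = 4): 0.5 + (256/70 − 1)/16 = 66.6%
- One block of 26 (b = 13): 0.5 + (67,108,864/10,400,600 − 1)/52 = 60.5%

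Simulation of 20,000 lists of 26 with randomly varying blocks gives about 69.8% for sizes 2/4/6 and about 67.4% for sizes 4/6/8.

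This strategy does not require knowing the block size; the running count on the list is enough. Every structure tried beats the 50% expected by chance.

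**Allocations known with certainty**

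If the block size is fixed and the recruiter knows it, the expected share known for certain is 1/(b + 1): 50.0%, 33.3%, 25.0%, 20.0% and 7.1% for blocks of 2, 4, 6, 8 and 26. The spread of 7% to 50% shows that no single figure can be given from the protocol.

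**Analyst blind**

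A record with T5, satisfaction or adherence data identifies TAB if those data exist only for TAB. The protocol is not consistent on this. Table 2 places T5 at week 58 for intervention families, whereas section 8.3 (Parents) names two assessment occasions and section 12.1 collects questionnaires at T2 and T4. The satisfaction scale is TAB-only by inference, because wait-list parents have had no program at T4. Section 11.3 plans adherence and compliance analyses. The protocol describes no order of data release that would keep such data from the analyst until the primary analysis is done.

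**The case against.** The strongest reply is that the essential concealment steps are present. An independent officer holds the list, consent and enrolment precede allocation, and disclosure follows it. Telling staff the arm after consent is ordinary in an open wait-list trial and never reveals that parent's own arm in advance. This stands, and it confines the risk to later parents on the same list.

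Block size is commonly withheld from a protocol, and that too stands: its absence is not a fault. A reader might infer that allocations are fully predictable, for example that 92, 61 or 46 of 184 parents (50%, 33.3% or 25%) would be known in advance. The documents do not support this. Those counts need a fixed block size known to the recruiter. Blocks of 4 and 6 do not divide a 26-space list, and three lists of 26 hold 78 places, not 184.

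Discretion is also narrower than it may look. Eligibility rests on fixed ASDS cut-offs. The judgements on ability to comply and on English or literacy sit under enrolment for screening, while randomisation typically comes three to four months after diagnosis. What remains is mainly the conduct and timing of the invitation. Nothing in the protocol shows that anyone steered entry.

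A reader might also conclude that the analyst blind is broken. That goes too far. A T2/T4 file with masked arm codes, analysed before other data are linked, could stay blind, and such arrangements may be in an SAP that is not shown.

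Finally, 7.4 already says that parents will know their arm once told, although it calls this partial blinding.

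**Conclusion.** Section 7.4 is wrong as written. Recruiters are not blind to client allocation, facilitators cannot be, and lack of access to the list does not secure what the section claims. The procedure does conceal each parent's own arm until after consent.

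The weakness is that upcoming allocations can be guessed at about 60% to 75%, against 50%. This assumes 1:1 permuted blocks within department and a recruiter who holds the full history of a list; if several recruiters share a list, each knows less. The rate measures opportunity. It does not translate into a size of bias in the PCL-5 comparison, which would depend on whether and how recruiters acted on a guess.

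The analyst point is secondary and conditional: if T5, satisfaction or adherence data are collected for TAB only and reach the analyst before the primary analysis, the declared blind is unprotected.

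**What to change.** 1. Have the research officer who already manages the list, or another team member outside recruitment, tell parents their arm and pass them to scheduling. Recruiters should receive no allocations while their list is open. The later contacts that reveal the arm, such as booking a TAB group or advising a wait-list parent of the start month (RCT Recruitment, item e), should be assigned the same way.
2. Use varying block sizes, withheld from recruiters, as a supporting measure only. If recruiters still learn allocations, this barely helps: about 69.8% for random 2/4/6 against 70.8% for fixed blocks of 4.
3. Reword 7.4 to claim concealment of upcoming allocations, and state plainly that facilitators and parents are not blind.
4. Run the primary T4 analysis on masked arm codes before any TAB-only data are released to the analyst.

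The cost is about 184 allocation calls (the recruitment total in Sample Size Estimation) moved to the research officer, who gains a parent-facing duty, plus protocol wording. No extra participants are needed. Timing limits the benefit. Groups were due to start in November 2014, and the primary outcome section already reports internal consistency from this study, so items 1 and 2 can apply only to parents not yet randomised. For parents already randomised, the wording should describe the procedure that was actually followed.
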